**Fig. 2 Fig2:**
[figure not shown]
Overview of the study scheme. During their baseline visit, participants will be randomized into either exercise or non-exercise group and either NR supplementation or placebo. After randomization, participants who were randomized into exercise group will receive their equipment and be oriented to the in-home exercise intervention. Participants who were randomized into NR group will receive NR daily at a dose based on body weight: 300 mg for individuals with weight 24 to < 48 kg, 600 mg for those with weight 48 to < 72 kg, and 900 mg for those with weight 72 kg or greater. After 8 weeks ($$\pm 1.5$$ weeks), all the participants will have their interim visit. After 16 weeks from the baseline visit, participants will have their final study visit. The figure was generated using Microsoft PowerPoint (Version 16.62)

### Study assessments {18a}

All study participants will complete a review of medical history, have their vital signs measured, and have laboratory assessments (CBC, CMP, HbA1c, lipid profile, blood to be banked for future ancillary metabolic and/or hormonal studies) (Table 3). Activity monitoring will be reviewed for seven days via an activity monitor (ActiGraph wGT3X-BT; ActiGraph Corp., Pensacola, FL) and, if assigned, the exercise training orientation will occur. After all study procedures are completed, supplement/placebo (NR/placebo) will be provided to the participant along with instructions and administration log. Specific to the primary and secondary outcomes, all participants will undergo the following assessments at the baseline and follow-up visits:

**Table 3 Tab3:**
[figure not shown]
Schedule of study procedures {13}

#### Dynamometry (hand grip, lower extremities)

Trained personnel will perform testing at CHOP and COH. A dynamometer (Takei Scientific Instruments Co., Ltd., Japan) will be used to measure instantaneous hand grip strength because in epidemiological studies this index of muscle strength has been shown to be associated with morbidity and mortality [28]. Three trials will be performed using each hand, and the maximum value will be recorded (N). The Biodex Dynamometer (Biodex Corp., Shirley, NY) will be used to measure muscular strength in the ankle and knee. Participant will perform isometric strength tests, with three repetitions performed at each position. A 5 s rest is given between repetitions. At each position, peak torque (N) will be recorded. References will be used to generate age- and sex-specific Z-scores [29].

*CrCEST MRI* is a non-invasive way to test skeletal muscle OXPHOS capacity [30]. With CrCEST, creatine content can be simultaneously measured in every muscle of the leg [31, 32]. CrCEST is used to determine the exponential time constant for the decline in creatine post-exercise (τCr) in each muscle of the calf (lateral gastrocnemius, medial gastrocnemius, and soleus) after an in-magnet standardized exercise on an MR-compatible. Prolonged τCr is suggestive of decreased OXPHOS capacity. In a “proof-of-principle” study using CrCEST at a 7 T MRI field strength [33], our team found that individuals with genetic diseases affecting mitochondria had significantly prolonged post-exercise τCr in the medial gastrocnemius muscle, indicating decreased OXPHOS capacity. Using CrCEST, we also found that habitual exercise duration is positively associated with muscle OXPHOS in individuals with genetic mitochondrial disorders [33]. In a separate study using CrCEST at 3 T, we found that decreased physical activity in individuals with Friedreich’s Ataxia, a neurological disorder, accounted for some of the difference in τCr in lateral gastrocnemius between individuals with Friedreich’s Ataxia and healthy controls [34]. We will use the same 3 T CrCEST to examine the effects of mitochondria-targeted interventions in the present study.

#### *CPET*

Maximal oxygen uptake (VO_2_max) derived from CPET represents the integrative efficiency with which oxygen is delivered (by the heart and vascular system) and used (primarily by skeletal muscle) to produce ATP to sustain exercise. Using near infrared spectroscopy, an association has been found between muscle oxygen extraction and CPET performance, specifically implicating muscle mitochondrial deficits in individuals with low VO_2_max [35]. Study participants will undergo an incremental symptom-limited CPET. After a 1-min warm-up at 0-Watt (W) workload, a ramp protocol of 5 or 10 W/min will be started and continued until maximal volition. Participants will be monitored for any potentially exercise limiting symptoms such as chest pain, signs of ischemia, or arrhythmias to develop or other indications for exercise termination to appear. Respiratory gas exchange measurements will be obtained breath by breath by a commercially available system at CHOP and at COH (Vmax 29C; Sensormedics, Yorba Linda, CA). VO_2_max will be recorded as the mean value of VO_2_ during the last 20 s of the test. Gas exchange will be measured continuously throughout exercise and for the first 2 min of recovery. The ventilatory anaerobic threshold will be detected by use of the V-slope and dual criteria methods. Musculoskeletal aerobic work efficiency will be calculated as the change in VO_2_ versus the change in work rate (ml O_2_/min/Watt) prior to anaerobic threshold (AT).

### Intervention components

#### *Exercise*

Participants randomized to exercise intervention group will be provided with the results of their CPET and dynamometry and receive an individually tailored exercise prescription, written by the exercise physiologist. The participant will be given a set of weights (varying depending on their weight and physical ability), a foldable exercise bike, (FB350 Folding Exercise Bike; XTERRA Fitness, Jonesboro, AR), resistance bands, a tablet (iPad 9^th^ Generation; Apple Inc., Cupertino, CA) to interact with the exercise physiologist, and a heart rate monitor (Polar Verity Sense; Polar Electro Oy, Kempele, Finland). Those randomized to the “no exercise” intervention group will be given the option to receive a similar individually tailored exercise prescription after the 16-week intervention is complete. The exercise prescription will be based on the results of their baseline assessments and account for any functional impairments. Each prescription will include aerobic and strengthening components designed to progress persons gradually towards the 150–300 min of aerobic activity (with duration depending on intensity) and twice weekly strengthening over 16 weeks that are recommended as part of public health guidance [36].

The exercise physiologist will supervise and provide guidance for the participants six times for the first two weeks, and then taper to twice a week for weeks 3–4, once for weeks 5–7, every other week for weeks 8–11, and to one time midway between weeks 12–16, each visit expecting to last one hour. During each session, participants will be asked to answer general physical and mental health questions. For aerobic training, the eventual intensity and duration goal will be for participants to train at 70–80% of peak heart rate 20–45 min 3–5 days/week [37]. Participants who have blunted heart rate responses to exercise will train using the Borg Rating of Perceived Exertion (RPE) scale [37]. For resistance exercises the goal will be a load/weight that results in fatigue after 3 sets of 10–12 repetitions on 8–10 exercises 2 days/week [38]. As many of these individuals will have chronic conditions and/or will be sedentary at baseline, the initial intensity and duration of the training may be much lower than typical sedentary individuals. In addition, progression toward and achievement of this goal will be heterogeneous. However, our tailored approach has great potential to impact our outcomes of interest since individuals who are sedentary [39] and those who are the most impaired may be positioned to achieve the largest incremental change [40]. Tailoring will be designed to allow each participant to start at a level reflecting their initial capacity, with personalized modifications as the study continues. Progression will also be tailored and be modified during the study to accommodate response to the intervention {11b}.

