## Methods/design

In this randomized controlled trial, we will prospectively enroll 80 participants status-post HCT at two sites, the Children’s Hospital of Philadelphia (CHOP) (Philadelphia, PA, USA) and the City of Hope Medical Center (COH) (Duarte, CA, USA). There will be 4 arms: exercise intervention with NR supplementation, exercise intervention with placebo, no exercise intervention with NR supplementation, and no exercise intervention with placebo. The individualized exercise intervention will occur in the home, overseen remotely via Telehealth by exercise intervention physiologists from St. Jude Children’s Research Hospital (Memphis, TN, USA) {9}. Participants who are randomized to the exercise intervention will be given the necessary equipment to participate either before they depart the site or by mail. Each participant will take part in the study for 16 weeks, with a total of three onsite in-person visits: one at baseline, one interim visit at week 8, and a final visit at the end of the 16-week intervention.

The primary objective of this study is to measure the effect of combination administration (NR + exercise) on skeletal muscle quality (strength along with mitochondrial OXPHOS capacity) in AYA HCT survivors {7}. Skeletal muscle quality will be measured by dynamometry, while OXPHOS capacity will be assessed through creatine chemical exchange saturation magnetic resonance imaging (CrCEST MRI). The secondary objective of this study is to measure the effect of combination administration (NR + exercise) on aerobic capacity (VO_2_max), as determined by cardiopulmonary exercise testing (CPET).

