The Safety Monitoring Uniform Report Form (SMURF) will also be used to assess NR specific side effects and will be administered at each in-person visit. The full SMURF contains a general inquiry, several questions about daily activities (e.g., sleep, appetite, energy level, bowel and bladder function), and modified queries specific to NR side effects. The general inquiry includes an open-ended question about any problems or complaints, as well as questions regarding the need for other medications and doctor or health care encounters since the last study visit. The next section includes 25 system-specific queries to ensure completeness. All new AEs will be documented. We will also check on the status of any previously reported possible AEs.

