In secondary analyses, we will seek to identify disease covariates and physiological factors (e.g., low muscle OXPHOS capacity at baseline) that are associated with treatment response [44]. With respect to additional outcomes, we anticipate that strength in other muscle groups, lower extremity muscle mass (measured via DXA), and muscle OXPHOS capacity (measured via CrCEST), will all increase in response to both interventions, and in statistical models will demonstrate independent contributions to the observed increases in muscle strength (primary outcome) and other key outcomes. In addition, blood metabolomics will show correlates of increased OXPHOS capacity (e.g., decreased acylcarnitine related to improved fatty acid oxidation capacity, organic acid profiles consistent with increased TCA cycle anaplerosis, and increased CoA species). Even if we do not detect changes in response to either of these interventions, our mechanistic assessments will produce an integrated understanding of the factors associated with low muscle mass, strength and OXPHOS in HCT survivors. The safety data will be an ancillary benefit to guide clinicians caring for HCT survivors who may be considering taking this supplement. The primary analysis will be repeated with each secondary outcome. Additional models will explore whether change from baseline can be explained by either baseline demographic or clinical covariates (age at randomization, sex, key clinical characteristics such as anthracycline and/or steroid exposure, age at HCT, TBI, GvHD grades II-IV, interval since HCT, and hypogonadism) or features of the intervention (final dose of NR, final training intensity in Mets per week). We will explore interactions between key variables and treatment arm. With respect to sex, we will include sex by treatment interactions in the model and explore the results of individual sex-stratified analyses, though we may lack adequate power to detect sex-specific differences {12}.

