With regards to ensuring adherence and compliance to the intervention, our team will be monitoring study participants in real-time via regular telephone check-ins and for those participating in exercise, via remote oversight, and thus be well-positioned to troubleshoot any barriers that may emerge during the conduct of the study. For NR/placebo, the investigative team will interview the adherence and intervene where necessary to ensure consistent administration of NR/placebo. Barriers to adherence can be reviewed at weekly check-ins and the interim visit. With regards to the exercise intervention, in-person orientation at the study site to exercise training using the in-home equipment will occur on the day of randomization, thus any functional or logistical limitations can be addressed in real time. To improve retention, we will offer participants randomized to the “no exercise” condition the opportunity to participate in in-home training after completion of the study {30}. Subjects who withdraw from the study will be recommended to update their medical history/concomitant medications, undergo physical exam, measure vital signs, test their clinical labs, get a DXA scan, get a 60 min MRI, perform a CPET, provide used/unused NR or placebo, and review adverse events as the early termination visit if both safe and feasible {18b}. In our team’s previous two studies of remotely supervised exercise interventions, we have demonstrated adherence rates exceeding 80% using similar procedures {11c}.

We will apply the insights gained from this trial to develop individualized, evidence-supported precision initiatives that will reduce chronic disease burden in high-risk cancer survivors. Our proposed trial is an important first step and will guide future interventions. We may also find that the benefits that accrue to skeletal muscle in response to skeletal muscle-focused interventions are recapitulated in other organ systems. For example, NAD^+^ precursors have impact on cardiac muscle, tissue that can also be adversely affected in cancer patients; in a preclinical model of dilated cardiomyopathy, NAD^+^ precursor attenuated the development of heart failure [50]. Additional metrics, such as circulatory power at peak exercise, can be measured to provide a non-invasive estimate of the circulatory system (i.e., heart rate, stroke volume, and systemic blood pressure) at peak exercise to explore such potential benefits.

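### Health questions are scheduled at about 16 supervised sessions in the exercise arms only, so non-serious adverse events may be detected more often there and adverse-event summaries that cross exercise levels may be biased

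*Protocol article*

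**What the plan says.** **Exercise arms.** The Exercise section sets supervised sessions of about one hour: "six times for the first two weeks, and then taper to twice a week for weeks 3–4, once for weeks 5–7", then "every other week for weeks 8–11, and to one time midway between weeks 12–16". It adds: "During each session, participants will be asked to answer general physical and mental health questions". Under Participants and randomization, only the outcomes assessor is blinded to exercise, so the staff who run these sessions know that allocation.

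**All arms.** Harms management states that the symptom form (SMURF) "will also be used to assess NR specific side effects and will be administered at each in-person visit". Methods/design lists three such visits: "one at baseline, one interim visit at week 8, and a final visit at the end of the 16-week intervention". Safety laboratory tests and a standardized symptom assessment also apply to everyone. The Discussion describes regular telephone check-ins for participants generally, with remote oversight on top for those who exercise. The use it gives for the calls is adherence: "Barriers to adherence can be reviewed at weekly check-ins and the interim visit".

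**Recording and use.** Harms management requires every adverse event to be entered in the study records and the case report form, with no exception by source. Under Meeting materials in the Appendix, the closed DSMB report lists adverse events by arm. Statistical considerations says "The safety data will be an ancillary benefit to guide clinicians caring for HCT survivors", and the rest of that sentence limits this to survivors who may take the supplement.

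**The concern.** Arms can be compared on adverse events only if events are looked for with similar intensity in each. Here one level of the exercise factor has a scheduled health inquiry at every supervised session, made by people who know the allocation. The other level has no described equivalent between visits. Mild or transient symptoms are the events most dependent on being asked about, so they are the ones most likely to differ in recorded frequency.

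The primary objective concerns the combination, and Stage 1 of the efficacy analysis sets each active arm against no exercise + placebo. The natural safety counterpart, exercise + NR versus control, crosses exercise levels. The DSMB will see the four arms side by side and must recommend continuing or terminating at each meeting. An excess of minor events in the exercise arms could then reflect how often participants were asked.

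**Working it through.** The article states no session total, adverse-event rate or detection probability, so there is no plan figure on this point to reproduce. The nearest stated figure is the sample size: 64 / (1 − 0.20) = 80, which agrees with Sample size and power. With four equal arms that is 20 per arm, or 40 at each exercise level.

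**Step 1. Supervised sessions (Exercise section).**
- Weeks 1–2: 6
- Weeks 3–4: 2 × 2 = 4
- Weeks 5–7: 3 if weekly, 1 if one session in total
- Weeks 8–11, every other week: 2
- Weeks 12–16: 1

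Total: 6 + 4 + 3 + 2 + 1 = **16**, or 6 + 4 + 1 + 2 + 1 = **14**. If the six sessions were per week, the total would be 12 + 4 + 3 + 2 + 1 = 22, a less natural reading.

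**Step 2. Common symptom form.** After baseline: week 8 and week 16, so 2 in every arm. On the structured instrument the arms are equal, 2 versus 2.

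**Step 3. All scheduled contacts after baseline.** Assume one check-in per week in every arm, in addition to any sessions: 16 calls, or 14 if visit weeks are skipped.

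| Sessions | Calls | Exercise | No exercise | Ratio |
|---|---|---|---|---|
| 16 | 14 | 16 + 2 + 14 = 32 | 2 + 14 = 16 | 2.00 |
| 16 | 16 | 16 + 2 + 16 = 34 | 2 + 16 = 18 | 1.89 |
| 14 | 14 | 30 | 16 | 1.88 |
| 14 | 16 | 32 | 18 | 1.78 |

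On the 22-session reading the ratios are 38/16 = 2.38 and 40/18 = 2.22. The contrast is roughly 2:1. Occasions on which a health question is actually described number 16 + 2 = 18 (or 14 + 2 = 16) versus 2, but that count puts informal session questions and the structured form on the same footing.

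**Step 4. What unequal detection would do (illustration; every input assumed).** Observed risk = true risk × probability of detection. With a true risk of 40% at both levels:
- Detection 90% versus 60%: 0.40 × 0.90 = 36% versus 0.40 × 0.60 = 24%, ratio 1.50. Among 40 per level, that is about 14 versus 10 participants (14.4 and 9.6).
- Detection 90% versus 80%: 36% versus 32%, ratio 1.13.
- Equal detection: ratio 1.00.

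**Step 5. NR versus placebo.** Within an exercise level both arms have the same sessions, calls and forms, and NR is blinded, so detection is the same by design. With assumed true risks of 40% (NR) and 20% (placebo), the observed ratio is 36/18 = 2.0 at 90% detection and 24/12 = 2.0 at 60%. The absolute differences are 18 and 12 percentage points. Setting those two differences against each other crosses exercise levels and would suggest extra NR harm with exercise where there is none.

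**The case against.** The strongest reply is that the comparison at risk is not planned. No section specifies an exercise-versus-no-exercise analysis of adverse events, DSMB listings are neither a test nor an estimate, and the stated use of the safety data is the supplement, for which the factorial design balances contact. That stands. It rules out calling a planned comparison biased, and it protects the NR contrast within each exercise level. It does not protect arm-wise listings read across exercise levels.

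A second reply is that the session questions are not called an adverse-event instrument, while the SMURF, with its open question, 25 system queries and recall back to the previous visit, is the same for all. This is also fair. But the recording rule has no exception by source, so a symptom mentioned in a session that meets the definition belongs in the record.

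A third reply is that the article is condensed and its schedule table is not shown, so check-in scripts may well include health questions. That is possible, and the point is therefore conditional.

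A reader might also infer three stronger things that the article does not support:
- That no-exercise participants are seen only at weeks 8 and 16, giving an 8- to 9-fold difference in inquiry. This leaves out the weekly check-ins.
- That the distortion can be sized, for example at 1.25 to 2.0 (1/0.8 to 1/0.5) from an assumed 50–80% recall. Neither recall figure comes from the document.
- That the rules on ceasing participation would act more often under exercise. Those rules concern Grade 3 or higher events, and nothing shows that finding such events depends on routine questioning.

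**Conclusion.** The point holds as a risk of unequal ascertainment. As written, scheduled health questioning is heavier in the exercise arms, is done by staff who know the exercise allocation, and has no described counterpart between visits in the no-exercise arms. Recorded non-serious events may therefore be more frequent under exercise at equal true rates, and summaries that cross exercise levels, such as exercise + NR versus control, may be biased. NR versus placebo within an exercise level is not biased by this route. A symptom missed between visits in the NR-alone arm is a loss of sensitivity that its control arm shares.

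The direction is clear but the size is not. Contacts differ by roughly 2:1 if weekly calls are made in every arm as assumed, and the 1.13 to 1.50 ratios above are illustrations only. The conclusion rests on two readings of the text: that health information from sessions reaches the adverse-event record, and that check-ins carry no health questions.

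**What to change.** 1. In Harms management and in the description of the check-ins, state that the same short set of health questions is asked at the existing weekly check-ins in all four arms, and that answers from check-ins and exercise sessions enter the adverse-event record.
2. Add one CRF field for how each event was elicited: visit form, check-in, exercise session or spontaneous report. This is hard to reconstruct later, so it should be in place from the first participant.
3. In DSMB tables and the final report, base adverse-event summaries across exercise levels on events from contacts common to all arms, and tabulate session-elicited events separately so that none is lost from safety review.

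The cost is slightly longer calls, more minor events recorded, one CRF field and one extra table. No new visits or staff are needed.
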